### Planned statistical analysis

The analysis will be focused on exploring the feasibility and acceptability of protocol implementation and refining the protocol of future RCT. The results from hypothesis testing will be treated as preliminary and interpreted with caution. The results of this study may provide a preliminary evaluation of any synergistic or additional effect, and of the non-inferiority of combined treatment of BVA and NSAIDs. All statistical analyses will be carried out using the Statistical Package for the Social Sciences (SPSS) for Windows version 18.0 and will be expressed by mean and standard deviation. The level of significance will be set at *P* < 0.05. For each outcome variable, an analysis of covariance (ANCOVA) will be performed on the data to adjust baseline characteristics. Trends over time and time-by-treatment interactions will be explored using a repeated-measures analysis of variance (ANOVA). A Chi-square test or a Fisher’s exact test will be performed to determine differences between groups and adverse effects, which will be recorded and described as a frequency and percentage. Fisher's exact test is used when the cell whose expected value is less than 5 is equal or more than 20%.

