### Outcomes

Assessment of neck pain-related dysfunction, pain and quality of life will be collected five times over eight weeks: at screening, visit two (baseline), four, six, eight (4th week assessment) and nine (8th week assessment) follow-up sessions. Medical history and sociodemographic characteristics, including age, gender, marital status, residence, occupation and education level will be taken from the screening visit. Any unpredicted, adverse events will be recorded at each visit (Table 1).

**Table 1 T1:** Schedule for data collection: outcome measures per visits

**Measures**	**Screening**	**Visit 2 (baseline)**	**Visit 4**	**Visit 6**	**Visit 8 (4th week assessment)**	**Visit 9 (8th week assessment)**
Sociodemographic characteristics	○					
Physical examination	○					○
Laboratory tests	○				○	
VAS for bothersomenesst of CNP	○	○	○	○	○	○
VAS for pain intensity of CNP	○	○	○	○	○	○
Neck disability index		○	○	○	○	○
EuroQol 5-Dimension		○	○	○	○	○
Beck’s depression inventory		○			○	○
SF-36		○			○	○
‘Skin roll’ test		○			○	○
Credibility test		○			○	
Adverse experiences*		○	○	○	○	○

*Adverse experiences will be monitored throughout the clinical trial.

CNP: chronic neck pain; VAS: visual analogue scale.

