### Primary outcome measurement

bothersomeness of chronic neck pain will be evaluated using the 10 cm visual analog scale (VAS) for CNP. Participants will be asked to report the degree of clinical severity and impact on activities of daily life experienced within the past week on a continuous discomfort scale of 0 to 10 (0, absence of discomfort; 10, the worst discomfort imaginable) [24] at screening, visit two (baseline), four, six, eight (4th week assessment) and nine (8th week assessment) follow-up sessions. The primary end point will be the VAS score at the four-week follow-up, one week after the completion of the three-week treatment session.

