### Sample size

Although there are previous researches on the effect of BVA and NSAIDs on chronic neck pain, there are insufficient data to estimate the clinical meaningful minimal change of the combined treatment of BVA and NSAIDs. This study is designed to provide the clinical evidence to estimate the sample size required for a full-scale RCT. As a pilot trial, we will recruit 60 patients into three parallel groups (BVA, NSAIDs or combined treatment). We will assess the impact of the interventions and the safety of combined treatment of different interventions on a limited number of patients.

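### The planned repeated-measures ANOVA would discard observed VAS scores from patients with incomplete follow-up; a mixed model would keep them in the longitudinal analysis (minor)

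*Protocol article*

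**What the plan says.** All references are to the protocol article.

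- **Longitudinal method (Planned statistical analysis):** "Trends over time and time-by-treatment interactions will be explored using a repeated-measures analysis of variance (ANOVA".
- **Group comparison of outcomes (same section):** a different method is named: "For each outcome variable, an analysis of covariance (ANCOVA) will be performed on the data to adjust baseline characteristics".
- **Weight of the tests (same section):** "The level of significance will be set at *P* < 0.05", and "The results from hypothesis testing will be treated as preliminary and interpreted with caution".
- **Primary end point (Primary outcome measurement):** "The primary end point will be the VAS score at the four-week follow-up, one week after the completion of the three-week treatment session".
- **Visits (Outcomes, Table 1):** the row "VAS for bothersomenesst of CNP" is marked at screening, visit 2 (baseline), visits 4 and 6, visit 8 (week 4) and visit 9 (week 8).
- **Size (Sample size):** "As a pilot trial, we will recruit 60 patients into three parallel groups (BVA, NSAIDs or combined treatment". No power, standard deviation or dropout rate is given.
- **Leaving the study (Withdrawal and dropout):** participation can end at any point, on refusal, withdrawn consent, a violation of the criteria or protocol, or too few completed sessions.

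The article does not say whether the ANOVA is univariate, sphericity-corrected or multivariate, or how missed visits are treated.

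**The concern.** Classical repeated-measures ANOVA needs a full row of scores for each patient. One missing VAS at visit 4, 6, 8 or 9 removes that patient's other scores too. The withdrawal rules make incomplete rows likely. A patient who leaves after visit 6 has given three usable scores (visits 2, 4 and 6), and none of them would count.

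Two things are at stake.

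- **Precision:** with about 20 patients per arm, each lost patient matters.
- **Bias:** other neck-pain treatments and analgesics are prohibited during the study, and a protocol violation can end participation. Departure linked to pain is therefore plausible, and the patients left in the analysis may not represent their arm.

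The Discussion asks whether repeated bee venom sessions have a cumulative effect and whether any benefit lasts. Of the methods named, this is the one directed at change over time.

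A second, conditional issue is that the univariate F test assumes sphericity. That is doubtful when scores far apart in time are less correlated than scores close together.

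**Working it through.** The plan states no figure to reproduce, so the check has two parts, both on stated assumptions.

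**1. Data loss**

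Inputs from the article: N = 60 and four follow-up VAS visits (4, 6, 8 and 9). Assumptions: baseline is complete, no values are imputed, and the missing rates are as shown.

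*Total dropout d.* Complete patients = 60 × (1 − d).
- d = 10%: 60 × 0.90 = 54.
- d = 20%: 60 × 0.80 = 48.
- If all of these patients left after visit 6, each would lose two observed follow-up scores as well as the baseline: 6 × 2 = 12 or 12 × 2 = 24 follow-up scores.

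*Independent missingness m at each follow-up visit.* Complete patients = 60 × (1 − m)^4. Observed follow-up scores = 240 × (1 − m).

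| m | Complete patients | Scores observed | Scores used by the ANOVA | Observed but discarded |
|---|---|---|---|---|
| 5% | 60 × 0.8145 = 48.9 | 228 | 48.87 × 4 = 195.5 | 32.5 (14%) |
| 10% | 60 × 0.6561 = 39.4 | 216 | 39.37 × 4 = 157.5 | 58.5 (27%) |

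A likelihood-based mixed model uses all the observed scores.

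**2. Error rate of the interaction test**

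Assumptions:
- Three arms of 20.
- Visit 2 is the first of the twice-weekly sessions, which puts visits 2, 4, 6, 8 and 9 at about weeks 0, 1, 2, 4 and 8.
- Screening is left out of the time factor.

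The univariate F then has (3 − 1)(5 − 1) = 8 and (60 − 3)(5 − 1) = 228 degrees of freedom. The departure from sphericity is ε = (tr S)² / [(k − 1) tr(S²)]. Here S is the covariance matrix of k − 1 = 4 orthonormal contrasts over the k = 5 visits, and ε = 1 means sphericity holds. For each structure, 8,000 trials were simulated with no treatment effect (Monte Carlo standard error about 0.3 points).

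| Assumed covariance | ε | Uncorrected F | Greenhouse–Geisser | Multivariate (Wilks) |
|---|---|---|---|---|
| Constant correlation 0.5 | 1.00 | 5.2% | 4.6% | 5.3% |
| Decay, 0.95 per week | 0.54 | 9.2% | 4.9% | 5.2% |
| Decay, 0.90 per week | 0.58 | 9.1% | 5.2% | 4.6% |
| Decay, 0.80 per week | 0.67 | 7.9% | 4.8% | 5.3% |
| Decay, 0.70 per week | 0.75 | 6.8% | 4.7% | 4.8% |
| Constant 0.3 plus 0.7 × decay 0.80 | 0.67 | 7.5% | 4.7% | 5.3% |
| Decay 0.80, SD growing from 1 to 1.8 | 0.60 | 8.3% | 4.6% | 4.9% |
| Equally spaced visits, AR(1) 0.7 | 0.69 | 7.8% | 5.1% | 5.0% |

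A separate run of 20,000 trials per structure gave 6.4%, 8.1% and 8.4% for the uncorrected F at weekly correlations of 0.6, 0.8 and 0.9.

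The first and last rows show the cause. The trial's own uneven visits give 5.2% when correlation is constant, and equally spaced visits give 7.8% when it decays. Falling correlation produces the inflation, not the spacing.

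**The case against.** The strongest reply is that the article names an ANOVA and no more. It does not commit to the uncorrected univariate F, and it does not say that incomplete patients are dropped. Sphericity corrections and missing-data handling are commonly left to an analysis plan, which is not shown, so their absence from a journal article is no fault. The analysis is also exploratory, in a pilot whose tests are declared preliminary. A mixed model has limits of its own: it relies on data being missing at random, and with baseline as a covariate it learns nothing from a patient who has no follow-up VAS.

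Most of this stands, and it rules out three stronger readings that a reader might draw.

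- **That the interaction test has an inflated error rate.** This needs the uncorrected F, which the article does not specify. Either standard alternative gives about 5%.
- **That uneven visit spacing breaks sphericity.** It does not do so by itself, as the constant-correlation row shows.
- **That the primary comparison is compromised.** It is a week-4 comparison by ANCOVA, which needs only baseline and week 4. A missed visit 4, 6 or 9 removes nobody from it.

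What the reply does not remove is the need for complete rows. That is a property of the method the article chose, not a missing detail, and neither a sphericity correction nor the multivariate test cures it.

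**Conclusion.** The point holds as a minor weakness of a named method. Applied as named, without imputation, repeated-measures ANOVA would discard scores already observed from any patient who misses a visit or leaves, and the article's own withdrawal rules make such patients likely.

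The amount cannot be derived, because no dropout rate is given. On the assumptions shown, 54–48 of 60 patients remain at 10–20% total dropout, and about 49–39 remain at 5–10% independent missingness per follow-up visit. Bias is possible if leaving relates to pain; its size depends on a dropout pattern that the article does not describe.

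The error-rate issue is conditional. The rate is about 6–9% instead of 5% only if the univariate F is left uncorrected and correlations decay over weeks 0–8. Both conditions are assumptions about this trial.

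**What to change.** Limit the change to the longitudinal analysis. Replace the repeated-measures ANOVA with a linear mixed model fitted by restricted maximum likelihood:

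- **Response:** VAS at visits 4, 6, 8 and 9.
- **Fixed effects:** treatment, visit, treatment-by-visit, visit-2 VAS, and visit-2 VAS by visit.
- **Covariance:** unstructured across the four visits (4 × 5 / 2 = 10 parameters), which removes the sphericity question.
- **Degrees of freedom:** Satterthwaite or similar.
- **Patients:** every randomised patient with at least one post-baseline VAS.
- **Report:** visit-specific treatment contrasts, including week 8, with 95% confidence intervals.

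Keep the week-4 primary ANCOVA as planned.

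The cost is a sentence or two of analysis wording and slightly more analysis work, with no new data. The trade-off is reliance on data being missing at random, which the report should state.

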### Randomization and allocation concealment

A total of 60 participants will be randomly assigned following simple randomization procedures, with a 1:1:1 allocation ratio. The randomization sequence will be generated by an independent researcher using a computerized, random-number generator through a Microsoft Office Excel 2007 software package. Opaque envelopes labeled by study patient number will be conveyed to the interviewer (CRC). The CRC will open the sealed envelopes and allocate participants into the predefined treatment arms. Allocation concealment will not be broken until the completion of the study. The random allocation assignment will be performed only after a participant is confirmed to be eligible and written informed consent has been obtained. Detailed information, including the treatment arm and randomization number from an individual participant will be recorded in the case report form (CRF) and randomization table.

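### Minor: for adverse effects, report between-arm risk differences with confidence intervals, because the planned test at about 20 patients per arm says little about the excess risk still possible

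*Protocol article*

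**What the plan says.** Safety of the combination is a stated aim in the Sample size section of the protocol article: "We will assess the impact of the interventions and the safety of combined treatment of different interventions on a limited number of patients". The size is set by pilot status, with no power claim and no adverse-event rate: "As a pilot trial, we will recruit 60 patients into three parallel groups (BVA, NSAIDs or combined treatment"). The Randomization section gives the split: "A total of 60 participants will be randomly assigned following simple randomization procedures, with a 1:1:1 allocation ratio".

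For adverse effects, the Planned statistical analysis section says "A Chi-square test or a Fisher’s exact test will be performed to determine differences between groups and adverse effects", and the sentence continues "which will be recorded and described as a frequency and percentage". The threshold is "The level of significance will be set at *P* < 0.05", with a rule for choosing between the tests: "Fisher's exact test is used when the cell whose expected value is less than 5 is equal or more than 20" percent of cells. The same section says the analysis focuses on feasibility, and that test results are preliminary and to be read with caution.

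The Safety section adds adverse-event and vital-sign reporting, and liver and renal function before and after treatment.

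**The concern.** A pilot that sets out to assess the safety of a combination should tell the planners of the full-scale trial how large an excess risk its data leave open. A test of no difference does not answer that question, and in arms of about 20 it will usually be non-significant even when the true risk is doubled. Percentages show the observed gap but not its uncertainty. The article's Discussion wants the findings to feed effect-size calculation for the later trial, which calls for estimates with intervals rather than P values. At stake is how informative the safety table is to whoever designs that trial.

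**Working it through.** **Inputs from the document.** 60 patients at 1:1:1, so 60/3 = 20 per arm expected (simple randomization does not guarantee it). Threshold 0.05. Fisher's exact test if at least 20% of cells have an expected count below 5, otherwise chi-square.

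**Assumptions.** Two-sided testing, no dropout, chi-square without continuity correction, and the comparator risks named below. The protocol gives no power or event-rate calculation for adverse effects, so there is no figure of its own to reproduce.

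**Step 1: what the test needs, with no event rate assumed.** Compare the combined arm with one comparator arm, 20 against 20. In a 2×2 table with m events in total, the expected event count per arm is m/2.

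- 2/20 vs 6/20: m = 8, expected 4, so two of four cells are below 5 and Fisher applies. P = 0.235.
- 2/20 vs 7/20: m = 9, expected 4.5, Fisher. P = 0.127.
- 2/20 vs 8/20: m = 10, expected 5, no cell below 5, so chi-square applies. X² = 40 × (2×12 − 8×18)² / (20×20×10×30) = 40 × 14,400 / 120,000 = 4.8, P = 0.028.
- 0/20 vs 4/20: Fisher P = 0.106. 0/20 vs 5/20: Fisher P = 0.047.

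Against 2/20, then, the combined arm must reach 8/20; against 0/20, it must reach 5/20.

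**Step 2: chance of missing a true doubling.** Miss rate = 1 − Σ Bin(a; 20, p) × Bin(b; 20, 2p), summed over all pairs (a, b) for which the protocol's own rule gives P < 0.05.

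| Comparator risk (assumed) | Combined risk | Missed |
|---|---|---|
| 5% | 10% | 98.3% |
| 10% | 20% | 92.0% |
| 20% | 40% | 71.6% |
| 30% | 60% | 53.7% |

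A single three-arm test with only the combined arm raised behaves much the same: 10/10/20% is missed 90.3% of the time and 20/20/40% is missed 71.7%. Very large differences are usually found: 10% vs 50% is missed 17.3% of the time.

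**Step 3: what an interval would show from the same data.** For 6/20 vs 2/20 the difference is 0.30 − 0.10 = 0.20. The 95% Wilson limits are 0.1455 to 0.5190 for 6/20 and 0.0279 to 0.3010 for 2/20. Newcombe's method gives:

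- lower limit = 0.20 − √[(0.30 − 0.1455)² + (0.3010 − 0.10)²] = −0.054
- upper limit = 0.20 + √[(0.5190 − 0.30)² + (0.10 − 0.0279)²] = 0.431

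That is 20 points, 95% CI −5 to 43. The P value of 0.235 conveys none of this.

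**Step 4: zero events.** With 0/20, the exact upper bound is 1 − 0.05^(1/20) = 13.9% (one-sided 95%) or 1 − 0.025^(1/20) = 16.8% (two-sided 95%).

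**The case against.** The strongest reply is that low power is the declared design. The article calls the trial a pilot, claims no power, limits the safety aim to a small number of patients, and tells readers to treat every hypothesis test as preliminary. It also reports counts and percentages, vital signs and laboratory results, so 6/20 against 2/20 would appear as 30% against 10%, and a reader could work out an interval. Interval methods and table layouts are often left to an analysis plan that is not shown here.

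Most of this stands. A reader might infer that the combination's safety is to be decided by this test, that P ≥ 0.05 would be read as safe, or that going on to the full-scale trial depends on it. The document supports none of these. No section states such a rule, the caution about hypothesis tests points the other way, and the test is one element of a largely descriptive safety assessment. Nor is it right that the sample cannot reject at all, as the 10% vs 50% case shows.

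What the reply does not remove is that the article has already named its between-arm method for adverse effects, and a better one is available from the same counts. The point asks for no more patients and no more power. The general caution tells readers to doubt the P value; it does not give them the excess risk still open.

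**Conclusion.** The point holds as a minor, cheap improvement. It is neither an error nor a contradiction in the protocol. The planned test at about 20 per arm is a weak guide to the combination's excess risk: the thresholds of 8/20 against 2/20 and 5/20 against 0/20 follow from the test rule and equal arms of 20, tested two-sided. The miss rates of about 98%, 92%, 72% and 54% also depend on assumed comparator risks of 5%, 10%, 20% and 30%, and no single figure in that range should be quoted as the trial's own. Unequal arms or dropout would generally lower power somewhat further.

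**What to change.** In Planned statistical analysis, for adverse effects:

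1. Report the number of patients with at least one event per arm, overall and by event category.
2. Give the risk differences combined minus BVA and combined minus NSAIDs with 95% confidence intervals (Newcombe or exact).
3. For event types with no events in an arm, give the exact upper bound, stating whether it is one-sided or two-sided.
4. Keep the chi-square or Fisher test as a supplementary line only.
5. State that P ≥ 0.05 will not be taken as evidence of comparable safety.

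The cost is a few sentences and some extra table columns, with no new data. The downside is a safety statement that looks visibly less reassuring, because the intervals will be wide.

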### Ethical approval and monitoring

This study has been approved by the KHUHGD IRB (KHNMC-OH-IRB 2012–019; April 2013). Study procedures and documents will be monitored by a qualified clinical research associate (CRA) from the Korea Institute of Oriental Medicine (KIOM).

### Data handling

Data obtained during the study will be confidentially treated according to the standard operation protocol (SOP) of the KHUHGD IRB, and will be stored in lockable cabinets. All data will be processed using the participants’ numbers which will be unrelated to participants’ personal information. Data will be compiled into CRFs and data integration will be thoroughly verified by independent researchers. Non-obvious errors or omissions will be put into data query forms, which will be used for the researchers’ workshop. Data will be gathered and summarized with respect to demographic baseline characteristics, effectiveness and safety observations.

## Discussion

This study will be conducted in a pragmatic setting which is considered appropriate to evaluate a combined treatment of BVA and NSAIDs as it is used in our usual practice [36]. According to the clinical experience, some patients with chronic pain tend to complain of more discomfort and disability than pain intensity itself [37]. Also, a previous study has shown that discomfort can be a more accurate responsive pain measure than pain intensity or other pain measures [38]. Considering the responsiveness study and clinical relevancy, clinical changes will be evaluated using the VAS for discomfort as a primary outcome measure.

The BVA increment protocol and the selected acupoints have been rigorously designed and chosen by a process of consensus among experts according to the Standards for Reporting Interventions in Clinical Trials of Acupuncture (STRICTA) [39]. All study procedures will be performed by delegated researchers trained to meet the study protocol and good clinical practice guidelines. In order to conceal the random allocation in this assessor-blind design, an independent assessor will be appointed and strictly educated to comply with the study protocol. Data will be compiled by an independent researcher, verified through a predefined database quality control procedure and analyzed by an independent statistician.

Although it is designed as a pilot study, every step of clinical study implementation will be rigorously conducted, monitored and supervised to ensure methodological integrity and scientific validity. The results from this pilot study will provide clinical evidence to evaluate feasibility and to develop a relevant RCT protocol on the combined treatment of BVA and NSAIDs for CNP patients. This study is designed to determine whether combined treatment of BVA and NSAIDs is beneficial shortly after the end of the treatment, whether a cumulative effect can be expected from BVA repetition, whether any possible clinical impact will persist, whether patients can take any synergistic advantages, and whether patients will be satisfied with this clinical setting. The findings in this study can be used to calculate effect size and analyze confounding factors for full-scale RCTs on the combined treatment of BVA and NSAIDs for CNP.

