Although combined treatments between conventional and CAM interventions have been frequently utilized, the effectiveness and safety has not been fully investigated in rigorously designed clinical trials. This study may be a preliminary evaluation of the non-inferiority of BVA against NSAIDs, and any synergistic or additional effect of each. The results from this pilot study will provide clinical evidence to evaluate the feasibility for full-scale randomized controlled trial (RCT) on combined treatment of BVA and NSAIDs for CNP.

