## Methods/Design

### Trial design

This is a randomized, assessor-blind clinical trial with three parallel arms (1:1:1 ratio) conducted at the spine center at Kyung Hee University Hospital at Gangdong (KHUHGD). We will compare the effects of BVA, NSAIDs and the combined treatment of BVA and NSAIDs in patients with CNP. The trial has been registered with the United States (US) National Institutes of Health Clinical Trials registry (NCT01922466) and has been approved by the Institutional Review Board (IRB) of KHUHGD (KHNMC-OH-IRB 2012–019). Outcome assessment and statistical analyses will be performed by independent researchers who are blinded to the patient assignment (Figure 1).

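### Synergy between bee venom acupuncture and NSAIDs is named as something the study will determine, but with no arm receiving neither treatment it cannot be established; only the add-on effects can

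*Protocol article*

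**What the plan says.** The Trial design section describes a "randomized, assessor-blind clinical trial with three parallel arms (1:1:1 ratio") and states the comparison: "We will compare the effects of BVA, NSAIDs and the combined treatment of BVA and NSAIDs in patients with CNP". The Interventions, Participants and Sample size sections name the same three groups. Every randomised patient receives at least one active treatment.

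Synergy appears in three places, with different force:

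- **Discussion (firm).** The sentence opens "This study is designed to determine whether combined treatment of BVA and NSAIDs is beneficial shortly after the end of the treatment" and goes on to list, as one of five items, "whether patients can take any synergistic advantages".
- **Planned statistical analysis (hedged).** "The results of this study may provide a preliminary evaluation of any synergistic or additional effect". The sentence before it says: "The results from hypothesis testing will be treated as preliminary and interpreted with caution".
- **Background (hedged).** The study may be a preliminary evaluation of, among other things, "any synergistic or additional effect of each".

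The planned models are a baseline-adjusted ANCOVA for each outcome and a repeated-measures ANOVA with time-by-treatment interactions. The article does not define synergy and gives no external figure for untreated patients.

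**The concern.** On the additive scale, synergy compares four means: combined, BVA alone, NSAIDs alone and neither. The trial observes three of them. A stated aim therefore depends on a quantity that the design never measures.

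The risk lies in what is reported and carried forward. If the combined arm does better than both single arms, the text invites the conclusion that the treatments act synergistically, although plain additivity would give the same result. The pilot's declared purpose is to shape a full-scale trial, so that conclusion, and the three-arm layout behind it, could pass into the next protocol.

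**Working it through.** The plan has no figure of its own to reproduce. The 60 patients are a pilot number, given without an SD, effect size or power. The question is whether synergy can be estimated at all.

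**1. Definition.** Write the mean outcome as μ + a·BVA + b·NSAID + g·(BVA × NSAID). Synergy is the interaction:

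g = combined − BVA − NSAIDs + neither.

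**2. Can the three arms estimate g?** The rows of the design matrix for (μ, a, b, g) are:

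| Arm | μ | a | b | g |
|---|---|---|---|---|
| BVA | 1 | 1 | 0 | 0 |
| NSAIDs | 1 | 0 | 1 | 0 |
| Combined | 1 | 1 | 1 | 1 |

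The rank is 3 for four parameters. Adding the row (0, 0, 0, 1) for g raises the rank to 4, so g is not estimable. This limit concerns identification and does not shrink as N grows. With a fourth arm (1, 0, 0, 0) the rank is 4 and g is estimable.

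**3. What the three arms do estimate.**

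- Combined − BVA = b + g, the effect of adding the NSAID to BVA.
- Combined − NSAIDs = a + g, the effect of adding BVA to the NSAID.
- BVA − NSAIDs = a − b.

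The first two are the additional effects that the text also mentions. Each mixes a main effect with the interaction, so neither isolates g.

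**4. Size of the ambiguity.** The document gives no expected effects, so these improvements in VAS bothersomeness at week 4 are assumptions: BVA 2.5 cm, NSAIDs 2.0 cm, combined 3.0 cm. With untreated improvement U,

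g = 3.0 − 2.5 − 2.0 + U = −1.5 + U.

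| Assumed U (cm) | g (cm) | Reading |
|---|---|---|
| 0 | −1.5 | less than additive |
| 1.5 | 0 | additive |
| 2.0 | +0.5 | synergy |

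The three observed means are the same in every row.

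**5. What can still be ruled out.** Suppose neither single treatment is worse than nothing. Then U is at most the smaller single-arm improvement, and

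g ≤ combined − BVA − NSAIDs + min(BVA, NSAIDs) = combined − max(BVA, NSAIDs).

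In the example the bound is 3.0 − 2.5 = +0.5 cm. If the combination is no better than the better single arm, the bound is zero or negative and synergy is excluded. If the combination is better, the bound is positive and the sign of g stays open.

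**6. Do the repeated measurements help?** Comparing changes from baseline recovers g only if untreated patients would not change at all. The protocol does not assume this, and natural course or regression to the mean would break it. The planned time-by-treatment interaction compares trajectories between arms and is not the BVA-by-NSAID interaction.

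**The case against.** **This is a pilot with hedged language.** The Background and analysis sections say only that the study may give a preliminary evaluation, and the tests are to be read cautiously. This stands as to tone: it would be unfair to read those two sections as a firm promise. Caution of that kind deals with imprecision, however, and does not make an unidentified quantity estimable. The Discussion sentence has no such hedge.

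**The word may be meant loosely.** Synergistic advantage could mean only that the combination beats either treatment alone, which the design can estimate. The article gives no definition, so this reading is possible for the Discussion. It is weaker for the Background and analysis sections, where synergistic stands beside additional as if the two differed. On the loose reading, pure additivity would be reported as synergy.

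**The illustration leans on an extreme case.** The value +0.5 cm needs U = 2.0 cm, at which the NSAID does nothing beyond no treatment. That is true of the endpoint, but any U above 1.5 cm gives synergy. At U = 1.75 cm, g = +0.25 cm, with separate effects of 0.75 cm (BVA) and 0.25 cm (NSAIDs).

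**Stronger readings that the documents do not support.** A reader might infer that the data can say nothing about synergy; step 5 shows that they can refute it under a mild assumption. A reader might also infer that the analysis will wrongly declare antagonism by setting the combined change against the sum of the single-arm changes. No such test is planned, so that would be a hypothetical misuse and not an error in this protocol.

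**Conclusion.** The point holds in a limited form. On the usual additive definition, this design cannot establish synergy at any sample size, although the Discussion says the study is designed to determine it. It could rule synergy out if the combination is no better than the better single arm and neither single treatment is worse than nothing. When the combination is better, which is where synergy would be claimed, additivity and synergy cannot be told apart. In the assumed example the interaction runs from −1.5 to +0.5 cm with identical observed data. Those figures are illustrative, and the identification result does not depend on them.

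Severity is moderate. Synergy is a secondary aim of a pilot. The primary endpoint, the randomisation, the data collection and the planned models are unaffected. It would go too far to conclude that the three-arm design is invalid for its other purposes: the additional effect of each component over the other alone is estimable.

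**What to change.** Remove the word *synergistic* from the Background, the Planned statistical analysis and the Discussion. State the aim as the additional effect of each component, combined minus NSAIDs and combined minus BVA, taken from the baseline-adjusted ANCOVA already planned. Add one sentence saying that synergy cannot be established without an arm receiving neither treatment, and that if it is a question for the full-scale trial, that trial needs a complete 2x2 design.

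The cost is wording only, with no added patients, visits or data. The article says the study began in July 2013, and the change can still be made before reporting. The downside is a narrower stated claim.

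A fourth arm in the pilot is not needed for this correction and would measure synergy only roughly. With 20 per arm, SE(g) = 2·SD/√20. For an assumed SD of 1.5 to 2.5 cm that is 0.67 to 1.12 cm, a 95% half-width of 1.31 to 2.19 cm.
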